### Exploring determinants of adoption, implementation and sustainment of SAIA-MOUD

Implementation outcomes—adoption, implementation, and sustainment—are important preconditions to ensuring attainment of desired service-level process and client-level health outcomes [39]. Though models of MOUD delivery in carceral and clinical settings are increasingly being designed and implemented, few studies are targeting development and testing of strategies that improve linkages between carceral and community settings of MOUD delivery. By describing to what extent SAIA-MOUD is adopted, implemented, and sustained, and identifying determinants (barriers and facilitators) of these implementation outcomes, we will endeavor to explain the linkage and retention in care results of this trial. Furthermore, results will inform the selection of core components and adaptations to SAIA-MOUD and serve as a common language to enhance transferability of findings to other contexts. Finally, we will document and describe adaptations to SAIA-MOUD to capture the dynamic process as the strategy evolves to better fit context.

#### Adoption

Adoption will be measured at the organizational level. For the purposes of this study, adoption will be defined as 1) identified staff from the target organizations (JHS, HMC-OTN, Pathways, Sound Health) attending SAIA-MOUD training, and 2) completing the first SAIA cycle. Based on previous SAIA trials and engagement with JHS, we expect high adoption of SAIA-MOUD (target: 80%). Describing determinants of adoption will provide actionable information to guide further intervention expansion. The Organizational Readiness for Implementing Change (ORIC) scale will be used to elucidate drivers of readiness to adopt SAIA-MOUD at the facility level, which will also be explored via qualitative evaluation of SAIA-MOUD guided by the Consolidated Framework for Implementation Research (CFIR).

*Organizational Readiness for Change* refers to the extent to which organizational members are psychologically and behaviorally prepared to implement organizational change, which affects decisions to adopt interventions like SAIA-MOUD [40]. ORIC is a 12-item Likert-type scale, broken into domains of change commitment and change efficacy that we have employed effectively in other SAIA trials to capture the extent to which organizational members are psychologically and behaviorally prepared to adopt and implement organizational change [27, 41]. The ORIC will be administered after the second month of SAIA-MOUD meetings to two managers and six frontline staff per organization (*n* = 32). Analysis will test whether sufficient inter-rater reliability and inter-rater agreement exist to aggregate individual responses to the organizational level [42–45]. If tests do not justify aggregation, we will use a measure of intra-organization variability in readiness rather than an organization-level mean in our analysis [43, 45]. The resulting analysis will provide readiness profiles for each organization as they initiate implementation, which will complement adoption, implementation, and effectiveness data in understanding the impact of SAIA-MOUD.

#### Implementation

Implementation fidelity is measured at the organizational level and will be assessed monthly using the SAIA monitoring system. Subsequently, implementation determinants will be explored via CFIR-guided qualitative inquiry with staff in both jail and referral MOUD clinics.

##### Implementation fidelity

A monthly implementation monitoring system will prospectively capture whether the individual SAIA-MOUD components (cascade analysis, process mapping and CQI cycles) were implemented each month, allowing us to describe implementation dose throughout the study [17]. Study team members will enter this information into a tablet-based RedCAP fidelity monitoring tool monthly (Table 3). Tracking measures of fidelity will provide an indication of SAIA-MOUD core components (*versus* peripheral/modifiable). Changes in fidelity patterns of over time in each of the SAIA-MOUD sites will be further explored via qualitative inquiry.

**Table 3 Tab3:** SAIA-MOUD fidelity monitoring tool

**Fidelity: **Was a SAIA cycle conducted with fidelity that month? (All must be YES)
Monthly SAIA meeting occurred (yes/no)
Workplan developed (yes/no)
Workplan was implemented fully or partially (yes/no)
**Fidelity with Quality: **Were workplans developed with quality? (All must be YES)
Micro-intervention is an appropriate solution for the problem (yes/no)
Micro-intervention is appropriate for the targeted MOUD cascade step (yes/no)
Micro-intervention is a clearly delineated task(s) assigned to a specific person/people (yes/no)

Micro-intervention is not an exact (verbatim) repeat of the previous month's past micro-intervention at the facility (yes/no)

##### Qualitative data collection and analysis

In-Depth Interviews (IDIs) and Focus Group Discussions (FGD) will be held with organizational staff in the final quarter of the intensive implementation period to examine the implementation process, define core SAIA-MOUD components, and describe determinants of success and failure in implementing organizations. A total of two staff in each implementing organization (eight total) will be interviewed, and four FGDs (one per organization) will be held. The CFIR, an established determinants framework, is well suited to this sub-aim, and will be used to develop interview and discussion guides to assess the multilevel factors that influence intervention implementation and effectiveness [46]. Interview and discussion guides will be developed using questions from the CFIR wiki guide to address selected constructs from the five CFIR domains. IDI and FGD guides will include questions adapted from the CFIR question bank to address the selected CFIR constructs (Table 4); the topics covered in each type of data collection will not differ, as we are interested in understanding group norms about each topic (via FGDs) and noting whether there are minority opinions (identified via IDIs). FGDs and IDIs will be conducted by an experienced facilitator (FGDs will be accompanied by a note-taker), audio-recorded, transcribed.

**Table 4 Tab4:** Ex. CFIR-guided questions

**Outer Setting**
***External Policies & Incentives***
What kind of county, state or national performance measures, policies, regulations or guidelines influenced the decision to implement SAIA-MOUD?
**Inner Setting**
***Structural***
What kinds of infrastructure changes are needed to accommodate SAIA-MOUD? Changes in scope of practice? Changes in formal policies? Changes in information systems or electronic record systems? What kind of approvals are needed?
**Process**
***Engaging—Opinion Leaders***
Who are the key influential individuals that need to be engaged with SAIA-MOUD implementation to make it work? What are influential individuals saying about the SAIA-MOUD?

FGDs will range in size from 7–10 participants, which is sufficient to generate conversation without being too large to become intimidating [47]. We will conduct IDIs with managers at each organization. By purposively holding FGDs for frontline staff separately from manager IDIs, we aim to identify opinions that lower ranking staff may feel uncomfortable sharing with their superiors, or issues related to staffing that higher ranking staff feel uncomfortable discussing with subordinates, which may be salient determinants of successful implementation in each site. The IDIs with managers will allow for exploration of the individual experience with the SAIA-MOUD, and reflection on adaptations experienced over the intensive intervention period. We expect that two IDIs and one FGD per organization will ensure > 80% of the staff at each site will be involved in providing input.

##### CFIR-guided analysis

Thematic analysis of qualitative data will follow CFIR domains and constructs to distinguish content and structure of the SAIA-MOUD training, materials, and mentorship *vs.* how SAIA-MOUD was received and implemented at the site. A two-step process will be used for analysis to identify drivers of implementation success and generate an in-depth understanding of implementation processes and predictors. First, two coders in a stepwise, iterative fashion will code the IDI and FGD transcripts and conduct content analysis within a deductive framework to identify key implementation themes (using selected CFIR constructs but allowing flexibility for other themes to emerge). Coding will be compared across pairs and differences discussed prior to final coding. Second, case memos will be written, and three analysts will assign ratings for each construct. Using a rating process previously applied to the CFIR, [48, 49] ratings will reflect the positive or negative influence (valence) and the strength of each construct. Constructs will be coded as missing too much data (M), not (0), weakly (+ 1/-1), or strongly (+ 2/-2) distinguishing low/high performance. Findings will inform recommendations for SAIA-MOUD, including identifying intervention core components, explaining intervention adaptation, and documenting lessons learned.

#### Sustainment

Moore et. al. defines sustainment as, “[a]fter a defined period of time, the program, clinical intervention, and/or implementation strategies continue to be delivered…while continuing to produce benefits for individuals/systems” [50]. Sustainment is a key construct of implementation science, and the field has called for an expanded research focus that moves beyond describing barriers to developing an evidence base on strategies to address barriers [39, 51]. We will describe sustained implementation of SAIA-MOUD and assess determinants of sustainment at each site using similar procedures described for the implementation period throughout the 12-month sustainment (non-intensive) period, including 1) describing fidelity to the monthly SAIA-MOUD protocol, paired with 2) qualitative inquiry (IDIs and FGDs) with site managers and frontline staff (using the same sampling, data collection and analysis techniques described above). Findings on sustained implementation of SAIA-MOUD without intensive support from research staff will complement initial effectiveness findings on client outcomes.

#### Describing adaptations

Adaptations to SAIA-MOUD will be prospectively documented during both the intensive and maintenance phases using the FRAME-IS, a framework developed to document modification to implementation strategies [52]. FRAME-IS is designed to monitor the component of the strategy adapted (content, training, context, etc.), the nature of the modification (tailoring, packaging, adding or removing elements, etc.), the goal of the adaptations (increase reach, adoption, acceptability, sustainability, etc.), and the level of the adaptation (organizational, implementer, clinician, etc.) By documenting adaptations and their motivations, FRAME-IS supports determining the processes or mechanisms through which implementation strategies influence implementation outcomes. We will incorporate FRAME-IS into the REDCap-based fidelity monitoring tool that is filled out monthly via tablet by those leading the SAIA cycles. There will be a checkbox to indicate if – during the month in question – there were any changes to the core SAIA-MOUD components (e.g. was cascade analysis, process mapping or quality improvement not conducted), and if so, the FRAME-IS questions will open to describe the goal, nature and content of these changes. At the end of the trial, data will be used to describe adaptations observed during both the intensive and non-intensive (maintenance) phases of the study.

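### The monthly form opens the FRAME-IS questions only on a change to a core SAIA-MOUD component, so other adaptations may go unrecorded in the prospective data

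*Protocol article*

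**What the plan says.** In the protocol article, Describing adaptations opens with a broad commitment: "Adaptations to SAIA-MOUD will be prospectively documented during both the intensive and maintenance phases using the FRAME-IS". It then sets out what the framework covers: "FRAME-IS is designed to monitor the component of the strategy adapted (content, training, context, etc", among others. It also lists the nature of the modification (tailoring, packaging, and adding or removing elements), its goal and its level.

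The same section then fixes how the form works. FRAME-IS is built into the monthly REDCap fidelity tool behind a checkbox. The rule for that checkbox reads: "any changes to the core SAIA-MOUD components (e.g. was cascade analysis, process mapping or quality improvement not conducted), and if so, the FRAME-IS questions". Once shown, the items ask only about the change that triggered them: what it was, of what kind, and for what purpose. At the end of the trial these data are to describe adaptations in both the intensive and the maintenance phase.

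The Implementation fidelity section says the monitoring system records "whether the individual SAIA-MOUD components (cascade analysis, process mapping and CQI cycles) were implemented each month". It adds: "Tracking measures of fidelity will provide an indication of SAIA-MOUD core components", as against peripheral or modifiable ones.

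**The concern.** The section states a wide purpose and a narrow entry condition. FRAME-IS is described as classifying changes to training and context, and changes made by tailoring, packaging or adding elements. The form as described asks the FRAME-IS questions only when one of the core components has changed, and the one example is a component that was not carried out. The follow-up items are worded to describe those changes, not others.

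The end-of-trial account of how SAIA-MOUD evolved is at stake. If the rule is followed as written, that account would lean towards omitted core activities. Changes to how staff are oriented, who takes part, how mentoring is done or where it happens would be thinly represented. The parts outside the named core would then look more stable than they were, in both phases.

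**Working it through.** No formula applies, and the plan gives no figure to reproduce. The check compares the stated scope with the stated trigger and then asks what else in the plan could record the same change.

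**Scope against trigger (Describing adaptations)**

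| Element | Scope given to FRAME-IS | What opens the questions |
|---|---|---|
| Object of change | Content, training, context and others | Core SAIA-MOUD components |
| Nature of change | Tailoring, packaging, adding, removing | Any change; non-conduct is the only example |
| Use | Describe adaptations in both phases | Same data |

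**Applying the stated rule to typical changes**

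1. Process mapping is not done in a month. This is the plan's own kind of example, and the questions open.
2. Orientation of new staff is shortened while all three components are done. No core component has changed, so the questions have no stated reason to open.
3. The people taking part, or the setting, change while all three components are done. The result is the same as in case 2.
4. Meetings move online. This is ambiguous: it could count as a change in how a core component is delivered, so two people completing the form could answer differently.
5. A monthly meeting does not take place. Table 3 (fidelity monitoring tool) records this whatever the checkbox says. Missed meetings are therefore not part of the gap.

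**Are cases 2 and 3 part of the strategy?** Yes. Process for introducing SAIA makes the 2-day orientation and the monthly visits part of delivery, and hands the visits to site teams during sustainment. CFIR-guided analysis treats training, materials and mentoring as SAIA-MOUD content.

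**Could another source record cases 2 and 3?**

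- Table 3 covers meetings, workplans and the quality of micro-interventions. It has no item on training, participants or setting.
- Manager interviews ask about adaptations and are not limited to core parts. For the intensive phase they take place in its final quarter, with two staff per organisation (eight in all), so they rely on recall and do not fill the monthly FRAME-IS fields.
- The Sustainment section repeats the interviews and focus groups with the same methods, which again gives retrospective coverage.

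**Extent of the form.** 4 organisations × (24 + 12) months = 144 organisation-months. This is how many monthly records the rule governs. It is not an estimate of how many adaptations are lost.

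**The case against.** The strongest case on the other side has four parts.

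- **The article paraphrases an instrument.** One sentence summarises a REDCap form, and the exact wording belongs to the form or the SOPs, which are not shown. That is a fair caution. But the article does more than leave the trigger open: it states one, and the one stated is narrower than the section's purpose.
- **The wording can be read generously.** The checkbox covers any change, and non-conduct is offered only as an example. This stands for changes in how a core component is delivered. It does not extend to training, participants or setting when the core components are untouched.
- **Recording an omission as an adaptation is no error.** The section lists removal of elements among the modifications FRAME-IS classifies, and the Implementation fidelity text says that conduct of each component is tracked monthly. This stands, and no fault is claimed there.
- **Naming core components in advance is not circular.** Starting from three named components and refining the list with evidence is reasonable. This also stands. The narrow trigger simply yields less prospective evidence about everything outside that starting list.

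A reader might infer that the study therefore cannot tell core from peripheral components. The article does not support this. It assigns that question to fidelity tracking (Implementation fidelity), to the interviews and focus groups (Qualitative data collection and analysis) and to the CFIR-guided analysis, not to the FRAME-IS form. A reader might also infer that non-core changes are scored as zero adaptations or lost altogether. No scoring rule is stated, and the interviews can recover some of them.

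**Conclusion.** The point holds as an internal mismatch. If the stated branching rule is followed, adaptations outside the core components may go unrecorded in the monthly prospective data, although the section gives FRAME-IS that scope and bases its end-of-trial description on those data. Prospective evidence on peripheral parts of the strategy is weakened but not eliminated.

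The share of adaptations affected cannot be derived from the article, and none is claimed. The conclusion rests on two assumptions: that the form follows the rule as written, and that some changes to training, mentoring, participants or setting will occur in months when all three components are done.

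The consequence is confined to a descriptive Aim 2 output. The linkage and retention analyses do not use these data. The correction is worth making because it is cheap and because details not captured in the month can later be sought only from memory.

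**What to change.** Widen the checkbox to ask whether anything about the SAIA-MOUD strategy changed that month, listing content, tools, meeting format, participants, training, mentoring and setting. Open the FRAME-IS questions on any yes. Add one item marking whether the changed part was a core component (including a component not conducted) or another part of the strategy, so that omissions and other adaptations can be described separately.

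If the form in use already asks the wider question, only the description needs correcting.

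The cost is one edit to the checkbox wording and REDCap branching, plus a few more minutes of data entry in months with a change. It is best done before monthly records accumulate, so that both phases are recorded under the same rule.

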### Estimating the cost and cost-effectiveness of SAIA-MOUD on improving equitable access within carceral and community settings, including costs of linkage across services

We will evaluate the cost-effectiveness of SAIA-MOUD from the county government, societal and healthcare sector perspectives.

#### Cost-effectiveness analyses

We will conduct both a cost-effectiveness analysis (incremental cost per additional person linked to care) and a cost-utility analysis (incremental cost per Quality-adjusted life-year (QALY) gained). Comparative effects between SAIA-MOUD and *status quo* will be estimated from our primary outcome of linkage to MOUD services post release from jail. Analyses will be conducted from the county, healthcare sector, and societal perspectives, and costs included in each perspective (Table 5).

**Table 5 Tab5:** Impact inventory of outcomes

Outcome	Included in Perspectives	Data Source	Analysis notes
SAIA-MOUD intervention	All	Time-motion studies	Micro-costing (see below)
Healthcare utilization and costs	All	Medicaid-data	Regression analysis
OUD-related	All	Medicaid-data	Regression analysis
OUD-unrelated	All	Medicaid-data	Regression analysis
Out-of Pocket	All	Medicaid-data	Regression analysis
Shelter/Respite Care	Soc, State	State Homeless Management Information Systems	Use unit cost approach
Criminal Justice Impact of Recidivism	Soc, State	State Criminal justice system	Direct costs of criminal activity to state
Societal Impact of Recidivism	Soc	Literature-based estimate	e.g., Property damage, pain, and suffering, etc
Net Productivity	Soc	No direct source	Will remain unmeasured
Welfare payments	State	State databases	Food and cash assistance
Life years	All	State Death Registry	1-Year survival analysis
Quality-adjusted life years	All	Medicaid-data	Quality of life weight based on diagnosed conditions in Medicaid

Costs for SAIA-MOUD will be measured using time-driven activity-based costing, [53] which assigns costs to personnel time required to complete implementation procedures. Procedures will be identified from the SAIA specification, [24] and time to complete these procedures will be gathered using a combination of participant self-report and supervisor report. Wage rates and overheads will be gathered from interviews with finance personnel. Costing will include all start-up and recurrent activities and measure resource use and costs from intervention design through sustainment at the clinics. Total costs will be divided by the total number of persons exposed to study sites implementing SAIA-MOUD to obtain an estimate of SAIA-MOUD cost per person.

Health state utilities used in cost-utility analysis will be estimated from diagnosed conditions in Medicaid data and from the published literature. We will calculate incremental cost effectiveness ratios (ICERs) by dividing the difference in costs between SAIA and *status quo* by the difference in outcomes. Uncertainty in estimates will be obtained via 1000 bootstrapped deviates. Cost-effectiveness acceptability curves will be used to communicate uncertainty to policymakers. Subgroup analysis will be carried out based on first-year versus second-year of SAIA-MOUD implementation, as well as covariates of interest (sex, race, ethnicity and housing stability).

#### Power

No power calculations are provided as Aim 3 procedures will rely on analyses articulated in Aim 1, together with cost data. As noted, uncertainty in estimates will be obtained via 1000 bootstrapped deviates.

### Trial status

Preparations for SAIA-MOUD initiated in January 2024. Initiation of SAIA-MOUD trial is planned for January 2025.

## Discussion

In this trial we will assess SAIA-MOUD, a novel and flexible implementation strategy to improve OUD screening, treatment and linkage to care for people exiting carceral settings. SAIA uses systems engineering tools to visualize care cascades, quantify gaps in care, and center patients’ experiences of care in quality improvement efforts. This approach allows health workers to prioritize interventions that can move patients more efficiently and equitably through critical care steps. SAIA is flexible and adaptable to local settings, empowering health care workers to test their ideas for optimization through a series of “micro-changes”. Rather than testing a single intervention that may become irrelevant after policy or technology changes, SAIA has longevity, as the approach is adaptable to the changing service landscape, which increasingly targets conditions like OUD.

We will employ innovative and robust implementation science methods to evaluate SAIA-MOUD. While more jails are adopting MOUD, much remains to be learned about addressing implementation challenges related to expansion of MOUD in carceral settings and linkage to clinical care upon re-entry [54]. Our design represents a novel application of SAIA because it will be implemented across levels of the health services, jail-based and community-based, with the goal of optimizing linkage to care after release, and ultimately decreasing opioid overdose in the vulnerable post-release period. Our design includes a range of implementation science methods including the ORIC scale [40] to assess facility readiness for SAIA-MOUD adoption, the CFIR to guide intervention planning, implementation, and address “what works, where and why”, through identification of implementation determinants to support further SAIA-MOUD implementation across diverse settings [46]. Adaptions to the SAIA-MOUD implementation strategy will be tracked throughout intensive and sustainment phases via FRAME-IS [52]. Additionally, cost effectiveness analyses rarely assess MOUD management strategies for individuals involved in the criminal legal system. This study will use a micro-costing approach to estimate the incremental cost per additional patient passing through the MOUD cascade from jail to clinical referral services. State of the art implementation science methods strengthen our evaluative framework for multi-level, theory-based adaptation of interventions.

